### Safety Assessments

We will collect data on related Adverse Events (AEs) on the Case Report Forms (CRFs). Where these events become Serious Adverse Events (SAEs) they will be reported in accordance with the CTRU’s and the sponsor’s Standard Operating Procedures (SOPs). These SOPs have been developed to comply with guidance from the National Research Ethics Service, which is a subdivision of the National Patient Safety Agency, and Good Clinical Practice (GCP). Site staff will be responsible for reporting SAEs; on identification they will complete an SAE form and send it to the CTRU and ensure that the local Principal Investigator has been informed.

Details of any related AEs will be recorded on the case report forms and participant completed questionnaires and reported periodically to the Sponsor, Data Monitoring Committee (DMEC) and the Trial Steering Committee (TSC). SAEs related to the intervention and unexpected will be reported Sponsor and expedited to the Research Ethics Committee (REC) within 15 days of becoming aware.

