### Objectives

The primary research question is does haemorrhoidal artery ligation have a lower recurrence rate than rubber band ligation when used to treat second and third degree haemorrhoids?

The secondary research questions are which of the two procedures is more cost-effective; which is least painful; which has fewest complications and which has the greatest effect on the patients’ quality of life?

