### Statistical and Health Economic analyses

Differences in the primary outcome, recurrence of haemorrhoids between the two treatment groups, will be analysed using logistic regression adjusting for sex, age at surgery and history of previous intervention as fixed effect covariates and surgeon as a random effect. This permits the calculation of odds ratios and their confidence intervals for the effect of HAL relative to traditional RBL adjusting for the effects of covariates and the clustering by surgeon. Further detailed analysis of haemorrhoid recurrence will be performed by analysing the length of time to recurrence under a Cox-proportional hazards model adjusting for the same covariates. The secondary outcome of pain, as measured on the visual analogue scale (VAS), with repeated measures will be analysed under a multi-level longitudinal approach adjusting for the same covariates. The secondary outcome of procedural complications elicited during the complications review or from the patient notes at 6 weeks and one year post surgery, will be compared between the two groups at each time point using Poisson regression which accounts for the essentially random nature with which complications arise, although care will be taken to note whether there is any clustering by surgeon. The emphasis of all analyses will be on estimating effect sizes of HAL surgery on recurrence rates and other outcomes in comparison to standard treatment with RBL, and as such appropriate confidence intervals will be reported for all estimates.

We will collect data as part of the trial that will allow us to conduct a full economic evaluation. The main economic analysis will focus on estimating the incremental cost per quality adjusted life year (QALY) of HAL versus RBL over the 12 month follow up period of the trial in: a) patients with new haemorrhoids; and, b) patients with recurrence following RBL. We will also present results in terms of the incremental cost per recurrence avoided.

The time horizon compares to 12 months used in an evaluation of SH versus RBL in patients with grade II haemorrhoids conducted alongside a pilot clinical trial
[26] and 3 years in a modelling study comparing SH and OH

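### Safety Assessments records and reports to the DMEC only adverse events already classed as related, and its sentences disagree on whether unrelated SAEs are reported

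*Protocol article*

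**What the plan says.** All the relevant rules are in the protocol article under Safety Assessments.

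- Collection of adverse events is limited to related ones, and the next sentence carries on from them: "We will collect data on related Adverse Events (AEs) on the Case Report Forms (CRFs). Where these events become Serious Adverse Events (SAEs".
- SAEs are introduced as a development of those same events: "Where these events become Serious Adverse Events (SAEs) they will be reported in accordance with the CTRU’s and the sponsor’s Standard Operating Procedures (SOPs".
- The site's duty is then stated for SAEs in general: "Site staff will be responsible for reporting SAEs; on identification they will complete an SAE form and send it to the CTRU".
- Periodic reporting returns to the related set: "Details of any related AEs will be recorded on the case report forms and participant completed questionnaires and reported periodically to the Sponsor". The sentence goes on to name the DMEC and the steering committee as recipients.
- Expedited reporting applies to a narrower group: "SAEs related to the intervention and unexpected will be reported Sponsor and expedited to the Research Ethics Committee (REC) within 15 days".

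The section does not say who judges relatedness. It refers SAE handling to procedures of the CTRU and the sponsor, which are not shown.

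Elsewhere, Objectives asks as a secondary question "which has fewest complications". Statistical and Health Economic analyses answers it with a Poisson regression of "procedural complications elicited during the complications review or from the patient notes at 6 weeks and one year post surgery".

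**The concern.** When relatedness decides whether an event is recorded at all, nobody can later check the decision. An event judged unrelated leaves no entry for the CTRU or the DMEC to look at again. When relatedness is a field on a form, the same judgement is made but can be reviewed.

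This matters more here than in a masked drug trial. Rubber band ligation is an outpatient procedure, and haemorrhoidal artery ligation needs an anaesthetic. Anyone who attributes an event while knowing the procedure has an obvious candidate cause, the anaesthetic, in one arm only. The same admission could be called related after one procedure and unrelated after the other.

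What is at stake is the DMEC's view of serious harm by arm while the trial runs. A site reading the first two sentences could properly withhold a form for a serious event that it thinks is unrelated. A site reading the third would send one. If sites follow different rules, the SAE counts are hard to interpret.

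**Working it through.** No arithmetic applies. The check is to ask what the section, read sentence by sentence, requires for each kind of event.

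**1. Non-serious event classed as related.** It is recorded on the CRF and reported periodically to the sponsor, DMEC and steering committee. The route is clear.

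**2. Non-serious event classed as unrelated.** The collection sentence ("We will collect data on related Adverse Events (AEs) on the Case Report Forms (CRFs") and the periodic-reporting sentence both omit it, so it has no stated route to the CTRU or the DMEC. The two sentences agree, so this is a stated choice and not an oversight.

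**3. Serious event classed as related.** Every sentence covers it. If it is also unexpected, it goes by the 15-day route as well.

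**4. Serious event classed as unrelated.** Here the sentences part:

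- *Sentence introducing SAEs:* the events that become serious are those just mentioned, namely the related ones. Read literally, a serious unrelated event is outside the SAE process.
- *Sentence on the site's duty:* SAEs are reported on identification, with no condition on cause. Read literally, the same event needs a form.
- *Sentence on expedited reporting:* it picks out SAEs that are both related and unexpected. If every SAE were related by definition, the first of those two conditions would add nothing. The wording therefore presupposes that unrelated SAEs exist.

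The section thus supports two incompatible rules for this event.

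**5. What the DMEC sees.** The only periodic feed described is of related adverse events. Even under the wider reading, in which an unrelated SAE reaches the CTRU on a form, the section does not say that the DMEC receives it.

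**6. Whether the comparison of complications uses this listing.** It does not.

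- Statistical and Health Economic analyses takes complications from the complications review or the patient notes, at 6 weeks and one year.
- The assessment schedule that follows Outcomes places the review interview at both times.
- Methods/design describes searches of hospital records, questions to consultants and GPs, and a 12-month telephone interview, to identify further treatment for recurrence or complications.
- Proposed sample size adds a review of hospital notes and a GP letter for patients who do not complete the 12-month follow-up.

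None of these is stated to depend on a relatedness judgement on an adverse event form.

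**The case against.** The strongest objection is that this is a condensed article which refers SAE handling to procedures said to comply with ethics-service guidance and GCP. Those procedures may already require every SAE to be reported, and two of the section's own sentences point that way. Both treatments are described as standard care, so limiting non-serious recording to related events is proportionate.

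Much of this stands. The limit on non-serious events is defensible and need not change. The unseen procedures may settle what sites do with SAEs. They do not remove the fault in the article, because its text states a rule for SAEs in one sentence and departs from it in others, and the DMEC feed is expressly limited to related events. That is wording on the page, not detail left out.

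A reader might infer four stronger points, which the documents do not support:

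- *That only related events can ever become SAEs.* The sentences on site duty and expedited reporting contradict this. The section is inconsistent, not uniformly restrictive.
- *That the filter corrupts the comparison of complications.* That analysis has its own sources, as shown above. The word procedural may imply some attribution to the procedure, but the article does not link it to the adverse event form.
- *That unblinded site staff are known to make the judgement.* The article does not say who judges relatedness and does not mention blinding. Knowledge of the procedure at the treating site is a reasonable inference from how different the procedures are, but no more. Participant questionnaires are also named as a place where events are recorded.
- *That the loss can be sized from the roughly 1% rates in Background, as 175 × 0.01 = 1.75 events per arm.* Those rates are for recognised complications, such as admission for severe pain after banding. Such events are the least likely to be called unrelated. The article gives no rate for the events at risk of exclusion and no misclassification rate.

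**Conclusion.** The point holds in a limited form. Safety Assessments makes relatedness a condition for recording adverse events and for reporting them periodically to the DMEC, and it gives conflicting rules for serious events classed as unrelated. The DMEC has no stated way to review such events.

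The consequence is for safety oversight during the trial. It is not shown to reach the primary outcome or the comparison of complications, and no number can be put on it from the documents.

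The conclusion rests on two assumptions. One is that whoever judges relatedness generally knows which procedure was done. The other is that the unseen procedures do not already override the article's wording. If they do require all SAEs to be reported, the correction is one of text only, apart from confirming that the DMEC receives them all. On either view it is a cheap improvement and not a threat to the trial's main result.

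**What to change.** Reword Safety Assessments so that:

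- all SAEs from randomisation to the 12-month follow-up are recorded and sent to the CTRU, whatever their judged cause;
- relatedness, and the role of the person who judged it, are fields on the SAE form and not conditions for completing it;
- the DMEC receives all SAEs by arm, with related SAEs shown as a subset.

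Recording of non-serious events may stay limited to related ones, and the 15-day expedited route for related and unexpected SAEs is unchanged. No separate list of named harms is needed, because the complications review already serves that purpose.

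Check the new wording against the CTRU and sponsor procedures so that sites work to one rule. If the trial has started, ask sites whether any serious event was withheld as unrelated, and collect those events retrospectively.

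The cost is an amendment to one section and to the SAE form, plus a modest number of extra SAE forms for unrelated events among 350 participants.

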### Objectives

The primary research question is does haemorrhoidal artery ligation have a lower recurrence rate than rubber band ligation when used to treat second and third degree haemorrhoids?

The secondary research questions are which of the two procedures is more cost-effective; which is least painful; which has fewest complications and which has the greatest effect on the patients’ quality of life?

### Outcomes

The primary outcome measure is ‘recurrence’, defined as the proportion of patients with recurrent haemorrhoids at 12 months, as derived from a telephone assessment in combination with GP and hospital records.

The trial is a pragmatic design with a dichotomous outcome. As no validated symptom score exists, we have based our definition of recurrence on Shanmugam et al.’s systematic review
[6] definition:

1. Cured or improved: Symptom free or mild residual symptoms but not requiring further treatment at the end of study period; or,

2. Unchanged or worse: No symptom improvement and requiring further intervention or suffered complication or deterioration of symptoms.”

This study will simplify Shanmugam's criteria into the following question, asked at 12 months by a research nurse:

‘At the moment, do you feel your symptoms from your haemorrhoids are:

1. Cured or improved compared with before starting treatment; or,

2. Unchanged or worse compared with before starting treatment?’

Any patient who answers ‘1’ but has required further treatment since the initial procedure will be reclassified as ‘2’, identified via hospital records, their consultant, their GP and patient questioning.

Secondary outcome measures:

1. Symptom score (adapted from Nystrom et al.
[23])

2. Health related quality of life (using the EuroQol-5D “The EuroQoL group”
[24])

3. Continence questionnaire (using the validated Vaizey Incontinence Score
[25])

4. Pain score (using a 10 cm visual analogue scale)

5. Surgical complications

6. Need for further treatment including details

7. Clinical appearance of haemorrhoids at proctoscopy following recurrence

8. Health care costs

9. Cost effectiveness

Eligible patients who have given written informed consent to participate in the study will undergo baseline assessment immediately before randomisation (Symptom score, EQ-5D, Continence questionnaire). After their procedure, patients will be asked to complete questionnaires one, seven and twenty-one days after surgery (EQ-5D, Pain score). At six weeks, further data will be collected at the routine follow-up clinic visits (Symptom score, EQ-5D, Pain score, Health and social care resource use questionnaire, Complications review interview, Need for further treatment questionnaire). Finally, one year after their procedure, they will be sent questionnaires (Symptom score, EQ-5D, Continence questionnaire, Health and social care resource use questionnaire, Complications review interview, Need for further treatment questionnaire, Recurrence) and be followed up by telephone. We will measure recurrence (the primary outcome) at 12 months.

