## Methods/design

The trial will be co-ordinated from the Clinical Trials Research Unit (CTRU) in Sheffield School of Health and Related Research (ScHARR). Delegated study staff located at individual centres will identify and consent potential participants. Potential participants will fall into three groups:

1. Patients presenting to the surgical outpatient clinic (SOPC) with symptomatic haemorrhoids that do not require further tests. This group will be identified by the clinical team from the GP referral letter and a patient information sheet sent to them prior to their clinic appointment. If they are willing to participate they will be consented and randomised when they attend the appointment.

2. Patients presenting to the SOPC with symptomatic haemorrhoids that require further tests to exclude other diagnoses. This group will be identified by the clinician at the clinic appointment and given a patient information sheet. They will undergo the necessary outpatient tests (usually endoscopy) and if negative (i.e. the symptoms are due to haemorrhoids) they will be contacted by the research nurse prior to attending their follow-up clinic appointment. They will then be randomised and consented when they re-attend the clinic.

3. Patients who return to SOPC following one unsuccessful RBL. They will be identified by the clinician at their first clinic appointment (when they have RBL) and given a patient information sheet. They will be contacted prior to a follow-up appointment (usually six weeks after treatment) by a research nurse. If they remain symptomatic and are willing to participate, they will be consented and randomised when they re-attend.

Thus, in each group, there is opportunity to provide the patient information sheet prior to a clinic appointment. Patients with investigations excluding pathologies other than haemorrhoids, and all those who have undergone rubber band ligation, will be contacted by the research nurse before the planned follow up clinic to ascertain whether they meet entry criteria and are interested in entering the trial. They will then be seen by the consultant and research nurse in clinic where recruitment and randomisation will take place.

After consent, participants will be individually randomised to HAL or RBL in equal proportion at all centres using a remote, web-based randomisation system.

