### Participants

The target population will be patients referred to collaborating centres for treatment of haemorrhoids. 350 participants will be recruited from surgical departments in up to 14 NHs hospitals. Adults aged 18 years or over with symptomatic second or third degree haemorrhoids, either presenting for the first time or after one failure of RBL will be eligible to take part in the research.

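### The primary outcome question does not say which treatment its reference point precedes, so patients who enter after a failed banding can answer it relative to a procedure outside the trial

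*Protocol article*

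**What the plan says.** The Outcomes section gives the wording of the question that a research nurse asks at 12 months. The two answers are "Cured or improved compared with before starting treatment" and "Unchanged or worse compared with before starting treatment". An answer of 1 is overridden in one situation: "Any patient who answers ‘1’ but has required further treatment since the initial procedure will be reclassified as ‘2".

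The Participants section admits patients "either presenting for the first time or after one failure of RBL". In Methods/design the third recruitment group is "Patients who return to SOPC following one unsuccessful RBL". Of these patients it says "They will be contacted prior to a follow-up appointment (usually six weeks after treatment) by a research nurse", and then "If they remain symptomatic and are willing to participate, they will be consented and randomised when they re-attend".

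The symptom score is taken immediately before randomisation and again at six weeks and one year (the timetable that follows the outcome list). The primary analysis is a logistic regression with history of previous intervention among its covariates (Statistical and Health Economic analyses).

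**The concern.** The primary research question is about recurrence after the trial procedure, so the natural comparison is with the patient's state just before that procedure. The question as worded does not fix this. A patient in the third group had a banding, usually about six weeks before the visit at which randomisation takes place. Asked a year later how things stand relative to the time before treatment started, that patient may think of the time before the first banding.

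Entry after a failed banding requires only that symptoms remain, not that the banding gave no relief. So a patient can be partly better at entry, gain nothing from the allocated procedure, and still truthfully choose option 1. If no further treatment follows, that patient counts as having no recurrence. At stake is some misclassification of the primary outcome, confined to one entry route.

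**Working it through.** **Which treatment is meant? The wording set side by side.**

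| Place | Term | Refers to |
|---|---|---|
| Methods/design, third recruitment group | treatment | the pre-trial banding |
| Statistical and Health Economic analyses, EQ-5D schedule | the treatment | the trial procedure |
| Methods/design, collection of further-treatment data | initial procedure | the trial procedure |
| Outcomes, reclassification rule | initial procedure | by the same usage, the trial procedure |
| Outcomes, the question itself | treatment | not specified |

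The article uses the same word for both reference points, and the question the patient hears does not choose between them.

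**Which safeguards apply?**

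- The reclassification rule catches a misread answer only if further treatment was required. A patient with unchanged symptoms and no re-treatment is missed, and that is a patient option 2 is there to capture.
- The covariate for previous intervention allows the recorded recurrence level to differ between entry routes. It does not restore a recurrence that was recorded as an improvement.
- The symptom score before randomisation has the right timing, but the primary question does not refer to it.

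**The plan's own figure.** Inputs from Proposed sample size: 30% recurrence after RBL, 15% after haemorrhoidal artery ligation (HAL), 80% power, 5% significance (taken as two-sided). With pooled variance and mean rate 0.225:

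n = [1.960 × √(2 × 0.225 × 0.775) + 0.842 × √(0.30 × 0.70 + 0.15 × 0.85)]² / 0.15² = 120.5, so 121 per group.

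This agrees with the article. After the 5% loss allowed for, 175 × 0.95 = 166.25 per arm. Power without clustering is then 90.9%.

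**Illustration of size.** Two inputs are assumed because the article gives neither:

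- s, the share of patients entering after a failed banding: 20-50%;
- m, the share of their true recurrences answered as improved and not caught by the further-treatment rule: 10-30%.

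Taking s and m equal in both arms, and the same recurrence rate in both entry groups, each arm's rate is multiplied by (1 − s × m). Power is Φ{[d√n − 1.960 × √(2p̄(1 − p̄))] / √(p₁(1 − p₁) + p₂(1 − p₂))}, where d = p₁ − p₂, p̄ is the mean of the two rates and n = 166.25.

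| s | m | 1 − s × m | RBL | HAL | Difference (points) | Odds ratio | Power |
|---|---|---|---|---|---|---|---|
| 0 | 0 | 1.00 | 30.0% | 15.0% | 15.0 | 0.41 | 90.9% |
| 0.2 | 0.1 | 0.98 | 29.4% | 14.7% | 14.7 | 0.41 | 90.2% |
| 0.5 | 0.3 | 0.85 | 25.5% | 12.75% | 12.75 | 0.43 | 84.4% |

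Between 2% and 15% of recurrences are lost. The risk ratio stays at 0.50 because both rates are multiplied by the same factor.

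**The case against.** **The question is asked in a trial setting.** A research nurse puts it a year after the trial procedure, following questionnaires timed from that procedure, and neighbouring text uses similar terms for the trial procedure. Many patients will take it as intended. The full protocol may also hold a call script, which an article would not reproduce. This stands as far as it goes: the phrase is ambiguous. A reader might infer that it *means* the time before the pre-trial banding, but the article does not say so. The reassuring terms, however, lie outside the words the patient hears, and those words are given as the question itself.

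**The path to error is narrow.** It needs a partial gain from a banding judged unsuccessful, a gain still felt more than a year later, no benefit from the trial procedure, the earlier reference point chosen, and no further treatment found in hospital records or through the consultant, GP or patient. This stands, and it keeps the likely size small.

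**Separate results for new and previously banded patients.** A reader might infer that comparing these groups becomes uninterpretable. No such comparison is planned. The economic analysis compares HAL with RBL within each group, and both arms of a group are asked the same question. Cost per QALY uses EQ-5D and not this question. Only the additional cost per recurrence avoided draws on it.

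**Bias towards one arm.** A reader might also suspect that a second banding feels like a continuation of the first while HAL feels like a new start, so that RBL patients choose the earlier reference point more often. If only RBL recurrences were lost, the same ranges would give 30 × 0.98 − 15 = 14.4 points down to 30 × 0.85 − 15 = 10.5 points, to the disadvantage of HAL. Nothing in the article supports or excludes a difference between arms, so this is conjecture and not part of the finding.

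**Conclusion.** The point holds as an ambiguity in the primary outcome. The reference point is not fixed for patients entering after a failed banding, and some who gained nothing from the trial procedure may be recorded as cured or improved. The further-treatment rule reduces this but leaves those who were not re-treated.

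If the arms read the question alike, the consequence is a modest dilution of the absolute difference, with little movement in the odds ratio, which is the planned effect measure. Across the assumed ranges power stays above the 80% design target, but these powers ignore clustering by surgeon, which would lower them. The size rests wholly on the assumed share and misreading rate. No stated figure is wrong, and the cost-per-QALY analysis is not affected. The change is worth making because it concerns the primary outcome and costs very little.

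**What to change.** Reword both response options so that each ends *compared with just before the procedure you were allocated in this study*, and have the nurse state the date of that procedure when asking. Do this before the first 12-month call, so that all patients hear the same question. The symptom score already collected at baseline and 12 months can serve as a consistency check on the answers, particularly for patients who entered after a failed banding.

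The cost is one phrase in the questionnaire and call script and one added line for the nurse. No new data are needed, and the sample size and analysis model are unchanged.

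### The longitudinal pain model adjusts for no measure of pre-treatment pain, although baseline EQ-5D is already collected: a modest, almost free gain in precision is forgone

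*Protocol article*

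**What the plan says.** All references are to the protocol article.

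- **Question.** Under Objectives, one of the secondary research questions is "which is least painful".
- **Instrument.** The Outcomes section lists among the secondary measures: "Pain score (using a 10 cm visual analogue scale".
- **Baseline.** The schedule at the end of Outcomes has patients "undergo baseline assessment immediately before randomisation (Symptom score, EQ-5D, Continence questionnaire". No pain score is in that list.
- **Follow-up.** After the procedure, "patients will be asked to complete questionnaires one, seven and twenty-one days after surgery (EQ-5D, Pain score". Then: "At six weeks, further data will be collected at the routine follow-up clinic visits (Symptom score, EQ-5D, Pain score", among other forms. Six weeks is the last time point with a pain score.
- **Analysis.** Under Statistical and Health Economic analyses, pain on the VAS "with repeated measures will be analysed under a multi-level longitudinal approach adjusting for the same covariates". The covariates meant are those of the primary model, described as "adjusting for sex, age at surgery and history of previous intervention as fixed effect covariates and surgeon as a random effect".
- **EQ-5D.** The same section confirms that EQ-5D is taken at baseline and states that the instrument reflects pain well. It gives EQ-5D a role in the QALY calculation and in exploratory work on utilities, but none in the VAS model.

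**The concern.** For a continuous patient-reported score, a baseline value of the same or a related measure is usually the first covariate to consider. Here the covariate set for pain is carried over from a binary recurrence outcome, and nothing in it says how much pain a patient had before treatment. Of the patient-reported scales in the outcome list, pain is the only one without a baseline value; symptom score, EQ-5D and continence all have one.

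Pre-treatment pain is plausible in this population. The Background counts pain on defecation among the surrogates of recurrent symptoms, and one recruitment route takes patients who are still symptomatic after a failed banding.

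At stake is the precision of the estimate for a named secondary question, in a plan that puts its emphasis on effect sizes with confidence intervals. A chance difference between arms in pre-treatment pain would also pass unadjusted into that estimate. The schedule half of the matter cannot be repaired later: an analysis plan can add a covariate that exists, but cannot supply a baseline VAS that was never taken.

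**Working it through.** **The plan's own figure.** The article gives no effect size, standard deviation (SD) or power for pain. Its one unadjusted sample size concerns recurrence (30% against 15%, 80% power, 5% significance, taken as two-sided). It reproduces with the pooled-variance formula:

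n = [1.96 √(2 × 0.225 × 0.775) + 0.8416 √(0.30 × 0.70 + 0.15 × 0.85)]² / 0.15² = 120.5, so 121 per group, as stated.

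Nothing there bears on pain, so no stated figure is contradicted. What follows only sizes the possible gain.

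**Inputs.**
- n = 175 per group (Proposed sample size).
- r, the correlation between the baseline pain measure and a later VAS score: not in the article. Assumed 0.1 to 0.5.
- A difference of 0.3 SD between arms: illustrative only.
- One time point, clustering by surgeon ignored.

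**Formulas.**
- Residual variance is multiplied by 1 − r², and the standard error (SE) by √(1 − r²).
- SE of the difference between arms, in SD units: √(2/175) = 0.107.
- 95% range of chance imbalance in the baseline measure: ±1.96 × 0.107 = ±0.21 SD.
- Shift in the unadjusted pain difference from an imbalance of that size: r × 0.21 SD.
- Power: Φ(0.3 / [0.107 √(1 − r²)] − 1.96). Without adjustment this is 80.1%.

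**Results.**

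| Assumed r | Variance reduction | SE ratio | Shift at an imbalance of 0.21 SD | Power for 0.3 SD (80.1% unadjusted) |
|---|---|---|---|---|
| 0.1 | 1% | 0.995 | 0.02 SD | 80.5% |
| 0.2 | 4% | 0.980 | 0.04 SD | 81.7% |
| 0.3 | 9% | 0.954 | 0.06 SD | 83.7% |
| 0.4 | 16% | 0.917 | 0.08 SD | 86.5% |
| 0.5 | 25% | 0.866 | 0.10 SD | 90.0% |

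With about 166 per group (175 less the 5% loss allowed for the primary endpoint), unadjusted power is 78.0%, rising to 81.7% at r = 0.3 and 88.4% at r = 0.5. The pattern is the same.

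**Where in the range.** One EQ-5D item is a coarse measure, so the low to middle rows are the more likely for it. Day 1 pain is probably dominated by the procedure, so r should be lower then than at 21 days or six weeks. A baseline VAS would probably sit higher than the EQ-5D item, but the article has no data on either.

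**The case against.** The strongest reply is that nothing here is invalid. Using the primary model's covariates for a secondary outcome is a sound randomised analysis, the schedule is consistent with itself, and an ordinary confidence interval already allows for chance imbalance. That stands, and it limits the point to efficiency.

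Three stronger readings are tempting, and the article does not support them:

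- **That the pain comparison is biased.** It is not. Pre-treatment pain is balanced in expectation by randomisation at every time point.
- **That the 21-day and six-week scores fail because procedural pain cannot be told from pain already present.** This affects how an individual score, or the level in one arm, is interpreted. The question asked compares the arms, and that contrast is unaffected. Nor would a baseline covariate split one patient's six-week score into two parts.
- **That baseline EQ-5D is wasted.** It feeds the QALYs, and the article plans to explore how EQ-5D relates to pain. It is absent only from the VAS model.

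It can also be said that the gain is unknown and may be small. The abstract names bleeding, irritation and prolapse as the haemorrhoidal symptoms, without pain, and the Background describes pain after banding as common for a few hours. Both suggest a low r, at least early on. That is why the range above starts at 0.1, where the gain is 1%. The percentages also describe a single time point and not the multi-level model as a whole, where the gain may differ.

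Finally, it may be said that covariates belong to the analysis plan, which is not at hand. But the article does state the covariate set for pain, and the schedule fixes what is collected. The point therefore concerns what is written, not missing detail.

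**Conclusion.** The point holds as a modest gain in precision on a secondary outcome. As written, the pain model contains no measure of pre-treatment pain and no baseline VAS is taken, although the trial holds a pre-randomisation measure that the article itself regards as reflecting pain well.

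The size depends wholly on an assumed correlation: 1% to 4% of residual variance if r is 0.1 to 0.2, 9% at 0.3, and 16% to 25% at 0.4 to 0.5. For the EQ-5D item alone, the low to middle part of that range is the reasonable expectation. These figures assume 175 per group, a single time point and no clustering.

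The conclusions on recurrence are untouched, and the planned pain comparison would remain valid if nothing were changed. The case for acting is that the covariate is already in hand and adding it has essentially no downside at this sample size.

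**What to change.** In Statistical and Health Economic analyses, extend the covariates of the longitudinal pain model to include the baseline EQ-5D pain/discomfort level as a fixed effect, alongside sex, age at surgery and previous intervention, and say whether the surgeon random effect carries over. The item is collected before randomisation, so allocation cannot influence it. The cost is one line of wording and no new data.

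Optionally, and only useful for patients not yet treated, add the same 10 cm VAS to the baseline questionnaire and use it as the covariate instead of the EQ-5D item. The cost is one extra item and a minor form revision. If recruitment is already under way, the EQ-5D item is the covariate available for everyone and should be kept.
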